### Randomization and allocation concealment

Participants will be randomly assigned to intervention and control groups using computer-generated randomization (http://www.randomizer.org/). A research assistant will handle the preparation of the envelopes by placing a carbon paper on top of the allocation paper, inserting both into a foil wrapper, and sealing them inside an envelope. Each envelope will be signed across the seal for authenticity. A total of 70 envelopes will be prepared with 35 allocated for the intervention group and 35 for the control group. Each envelope will be manually labelled as either “intervention” (1) or “control” (0). Once prepared, all 70 envelopes will be thoroughly shuffled to ensure randomness. A unique number sequentially from 1 to 70 will then be marked on the front of each envelope using a pen. The carbon paper inside will transfer this number onto the allocation paper. Finally, the envelopes will be placed in a plastic container in numerical order and ready to be used for the group allocation. After recruiting a participant, the research assistant will sequentially open an envelope, with the number inside indicating the participant’s group assignment. In this study, neither the participants nor the research assistants will be blinded to group assignments; however, the data collector will be blinded to group assignments to minimize measurement bias.

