### Data collection and monitoring

Data collection and monitoring of participants’ progress will be conducted by trained research assistants who are physiotherapy students or qualified physiotherapists. While the delivery of the intervention will be done by the main researchers (First and third author) assisted by the research assistants. Before participant recruitment, to ensure consistency across different settings, the research assistants will undergo thorough training, including understanding the protocol of the PTICOPE and hands-on practice with all outcomes measures for measuring the IC, guiding participants through tailored exercises, and providing education on self-management strategies. The research assistants will also monitor progress, adjust interventions to individual needs with guidance from the main researchers.

Recruitment of study participants will be conducted at three PAWE after obtaining research ethics approval and permission from the person in charge of the centers. The researchers will invite all participants who are members of the PAWE via letter of invitation, flyers, and verbal invitations. Those who volunteer to participate will be invited to a briefing session to inform the purpose and procedure of the study. Participants who provided informed consent and fulfilled the inclusion criteria will undergo the 12-week RCT. All participants will undergo an evaluation of the sociodemographic data, and primary and secondary outcomes at baseline. Evaluation of primary outcomes will be repeated at week 4, week 8, and week 12. Evaluation of secondary outcomes will be repeated at week 12. Once baseline data has been collected, participants will be randomly assigned to either the intervention or control group. The intervention group will receive the PTICOPE module in the form of a workbook and include comprehensive guidance on its use to support IC. In contrast, the control group will receive general information on the importance of maintaining IC, along with health education on the importance of exercise, and healthy diet, and self-care management which include recommendations to seek relevant healthcare services based on their baseline IC measurements.

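### As described, the carbon paper ties each allocation slip to its envelope but not to a participant, so a departure from the allocation order would leave no trace

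*Protocol article*

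**What the plan says.** The section on randomization and allocation concealment gives the envelope steps in order. An assistant lays carbon paper over the allocation slip, wraps both in foil, seals them in an envelope and signs across the seal. The 70 envelopes (35 per arm) are shuffled. Then "A unique number sequentially from 1 to 70 will then be marked on the front of each envelope using a pen", and "The carbon paper inside will transfer this number onto the allocation paper". After that, "the envelopes will be placed in a plastic container in numerical order and ready to be used for the group allocation".

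For the allocation itself the section says: "After recruiting a participant, the research assistant will sequentially open an envelope, with the number inside indicating the participant’s group assignment". On blinding, it says that "neither the participants nor the research assistants will be blinded to group assignments", while the data collector is to be blinded.

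The section on data collection and monitoring adds the participant flow. "Those who volunteer to participate will be invited to a briefing session"; consent, the eligibility check and baseline assessment follow. Then: "Once baseline data has been collected, participants will be randomly assigned to either the intervention or control group". The same section says that research assistants help the main researchers deliver the intervention.

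**The concern.** Carbon paper in a sealed allocation envelope is most useful when the participant's identifier is written on the outside before the seal is broken. The slip inside then carries a record, made blind to the arm, of whom that allocation was for. Here the only thing described as reaching the slip is the sequence number, written before the envelope is assigned to anyone. The carbon is in place but is not used to commit a participant to an envelope.

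This matters when more than one enrolled person is waiting. If an envelope were opened and its arm seen before it was settled whose envelope it was, two participants could be exchanged and the slips would look the same either way. The assistants are unblinded, and the one opening envelopes may also help deliver the programme. The resulting selection bias would come from prognosis as judged by staff, in an open trial with 35 per arm. The gap is separate from foreknowledge of the next allocation: it would remain even if the contents of every sealed envelope were impossible to guess.

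**Working it through.** No figure in the article depends on this point, so there is none to reproduce beyond 35 + 35 = 70 envelopes, which agrees. The check is of the sequence of steps, followed by an illustration of size.

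**Sequence of steps**

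1. Preparation: slip, carbon, foil, seal, signature, shuffle, number. The carbon copies the number. Result: slip linked to envelope.
2. Storage: numerical order. Result: the order of envelopes is fixed.
3. Enrolment: consent, eligibility, baseline data. Result: participant ready for allocation.
4. Allocation: next envelope opened, and its content is the participant's group.

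Between steps 3 and 4, neither section describes an entry that links participant and envelope before opening. If step 4 is followed, the next participant receives the next envelope and nothing is left to choose. If it is not followed, the slip shows only a number and cannot reveal an exchange.

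**Illustration of size**

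Input from the sample size section: SD 2.5 for the primary outcomes, with a 1-point change on the Short Physical Performance Battery (SPPB) cited as clinically meaningful. Assumptions not in the article: all 70 participants wait in 35 pairs; scores are normal; and in a share s of pairs an assistant sees both allocations and, if the arms differ, gives the intervention to the fitter person.

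- Expected difference between the fitter and less fit member of a pair: 2 × SD/√π = 2 × 2.5/1.772 = 2.82 points.
- Chance that two consecutive envelopes hold different arms: 35/69 = 0.507.
- Expected arm gap: s × 0.507 × 2.82 = s × 1.43 points.

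| Share s of all waiting pairs | Formula (points) | Simulation, 10,000 runs (points) |
|---|---|---|
| 0% | 0 | 0 |
| 10% | 0.14 | 0.14 |
| 25% | 0.36 | 0.36 |
| 50% | 0.72 | 0.73 |
| 100% | 1.43 | 1.44 |

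The base of the percentage matters. If one-per-arm pairs that were interfered with make up 10% of all 35 pairs, the factor 0.507 drops out and the gap is 0.10 × 2.82 = 0.28 points.

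For comparison, the standard error of a chance baseline gap with 35 per arm is 2.5 × √(2/35) = 0.60 points.

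**The case against.** A reader might infer that the procedure lets an assistant decide, after seeing the arm, who receives it. The text does not support that. The envelope is opened after a participant has been recruited and baseline data collected, envelopes are taken in numerical order, and the content is that participant's group. An exchange would be a breach of the rule, not a use of it. This part of the objection stands.

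Nor is the carbon useless. It ties each slip to a numbered, signed envelope, so it helps to expose slips moved between envelopes. It gives no protection against an exchange between participants.

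It is also too strong to say that no paper trail would exist. The article condenses a full protocol, which may contain an enrolment log or an entry made before opening. What the article does state is what the carbon carries, and that is the envelope number. If the full protocol has it carry a participant identifier, the article's description needs correcting.

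The waiting queue is an assumption. The briefing session makes it plausible, but the article does not say that several people are unallocated when an envelope is opened.

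Finally, one could say that analysis would deal with it. SPPB is measured before assignment, so a gap would be on record, and a constant baseline difference largely drops out of the planned time-by-group interaction. That is fair for measured baseline SPPB, although gaps of 0.14 or 0.28 points lie well within the chance standard error of 0.60 and would not draw attention. It does not cover selection on prognosis that baseline scores miss, such as expected adherence or rate of decline.

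**Conclusion.** The point holds in a limited form. The carbon step, as described, records the envelope and not the participant. The allocation rule is sound if followed, but the described procedure neither prevents nor would reveal a departure from it.

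The size of any bias is unknown, and it is zero without interference. The figures of about 0.14 points (10% of all waiting pairs) and 0.28 points (one-per-arm pairs interfered with as 10% of all pairs) rest on the assumed pairing, the assumed rate and the stated SD of 2.5. They are illustrations, not estimates, and both are below the 1-point threshold. They also describe a gap in baseline SPPB, which the interaction test would largely absorb. The reason to act is possible selection on unmeasured prognosis, which the article gives no means to quantify.

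This is a nearly free improvement to a step already in the plan. It is not evidence that the allocation is open to choice as written.

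**What to change.** Replace the sentence on what the carbon transfers, and extend the opening step, along these lines:

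*Once consent, eligibility and baseline data are complete, the participant's study ID (issued in order of consent) and the date are written on the next sealed envelope, so that the carbon copies them to the allocation slip. Only then is the envelope opened. Envelopes and slips are kept and reconciled with the enrolment log.*

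If the full protocol already has such an entry or log, correct the article's description to match. The change uses the carbon paper, foil and numbered envelopes already specified. It costs a few seconds per participant and does not affect the sample size, the analysis or the intervention.

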### Intervention

#### Development of PTICOPE module.

The development process of the PTICOPE module includes two main steps: (1) creating the PTICOPE module based on the WHO-ICOPE guidelines and evidence gathered, and (2) validating the module through content validation (with experts) and face validation (with older adult participants). This approach is designed to enhance IC in older adults through a tailored, person-centered framework. Initially, data from literature and systematic reviews are gathered to identify factors and interventions related to IC decline. We also adopt the construct of the Health Belief Model (HBM) to guide the development of the module as shown in Table 1. The HBM recognizes and addresses the social context in which health behaviours take place that can be incorporated into the PTICOPE intervention to increase knowledge of health challenges, enhance perceptions of personal risk, encourage actions to reduce or eliminate the risk, and, eventually enhance the sense of self-efficacy to continue changing [15,16].

**Table 1 pone.0318513.t001:** The application of the health belief model in the PTICOPE module.

HBM Constructs	Features of PTICOPE
Perceived Susceptibility and Severity	Participants will be educated about the importance of intrinsic capacity (IC) and how its decline can impact activities of daily living, independence, well-being, and quality of life. The participants will be informed of their assessment findings to help them recognize their vulnerability to IC decline.
Perceived Benefits	The participants will be informed about the benefits of the PTICOPE intervention in enhancing the IC domains, not only through the exercises and healthy diet but also the indirect effects of seeking personalized care from other healthcare disciplines. In the long run, these practices can prevent disability, promote independence, and support active aging.
Perceived Barriers	Through ongoing monitoring of the PTICOPE intervention via WhatsApp and face-to-face meetings, the researchers and participants will address the potential barriers that limit their adherence to exercise and dietary advice. Through discussion between the researchers and participants, guidance and ways can be suggested to overcome the barriers.
Cues to Action	The researchers will remind the participants regularly to continue achieving and revising the goals that they have agreed to at the beginning of the intervention.
Self-Efficacy	The elements of the PTICOPE module include strategies for managing health and enhancing IC through goal-setting, and feedback from the researchers. The researchers will use techniques such as demonstration and positive reinforcement during the weekly meeting and communication through WhatsApp. Positive reinforcements from the researchers may build the confidence of the participants to continue following the recommended activities in the PTICOPE module.

The contents of the PTICOPE workbook will be tailored to the Malaysian context by aligning with the intervention and management suggested by WHO-ICOPE (Table 2), featuring contents that are educational, culturally relevant, practical exercises with self-tracking tools to support older adults’ intrinsic capacity and ease of understanding. The input from experts, among other include physiotherapists, geriatricians, psychologists, occupational therapists, dieticians, and input from practitioners and educationists in the validation process ensure collaborative efforts from several healthcare disciplines that can address all aspects of aged-care. The workbook is designed with interactive features like visual aids and graphic instructions to enhance participants’ engagement, making the workbook an effective and user-friendly tool for older adults.

**Table 2 pone.0318513.t002:** Contents of the PTICOPE module.

Intrinsic Capacity Domain	Activities/Interventions	Advice	Goal Setting
Locomotor	Balance exercises (e.g., tai chi, single-leg stands) three times weekly. Strength exercises using resistance bands. Flexibility exercises like stretching or yoga.	Encourage daily low-impact physical activities like walking at moderate intensity. Recommend supportive footwear and safety modifications (e.g., handrails).	Weekly mobility goals tailored to ability levels, such as aiming for 10-15 minutes of walking daily, gradually increasing time and intensity.
Vitality	Nutritional guidance with a focus on protein intake, hydration, and key vitamins Monthly meal planning assistance. Weekly hydration reminders.	Recommend balanced meals with lean protein, vegetables, and hydration goal (e.g., 8 glasses daily). Provide strategies for appetite stimulation if needed.	Daily dietary and hydration goals; track nutritional intake using a simple chart or apps.
Psychological	Mindfulness practices (e.g., breathing exercises, meditation). Stress-reduction techniques such as guided imagery. Weekly community engagement activities (e.g., group walks).	Recommend social interactions, like weekly calls or outings with family/friends. Encourage hobbies that provide cognitive engagement (e.g., gardening, reading).	Set personal well-being goals such as attending a social event weekly or completing a relaxation activity daily.
Cognitive	Memory exercises (e.g., word games, memory matching). Problem-solving tasks (e.g., puzzles, strategy games). Use of cognitive apps like Lumosity for 10-15 minutes daily.	Recommend engagement in cognitive activities (e.g., puzzles) for mental stimulation. Encourage reading or learning a new skill.	Set weekly cognitive goals (e.g., complete a puzzle or read a chapter daily).
Hearing	Whisper test or audiometry screening annually. Environmental adjustments (e.g., using hearing aids, minimizing background noise).	Advise on ear care (e.g., avoid loud environments, use ear protection if needed). Encourage social support for improved communication.	Aim to maintain current auditory health or improve understanding with assistive devices. Set quarterly hearing check-ins.
Vision	Vision exercises to reduce eye strain. Regular eye exams (annually). Home environment adjustments (e.g., improve lighting).	Recommend eye protection (e.g., sunglasses outdoors). Suggest routine visual health monitoring, such as checking for blurriness.	Set visual health goals (e.g., reduce screen time, follow up on eye examinations).

Moreover, the contents of the module are also aligned with WHO’s 13 ICOPE recommendations, which are customized to meet the specific needs of older adults in the respective settings [12]. Table 2 outlines the proposed contents of the PTICOPE module.

#### Validation of the PTICOPE module.

The validation of PTICOPE includes a thorough content validation phase involving 12 multidisciplinary healthcare experts, representing fields such as occupational therapy, physiotherapy, geriatrics, family medicine, public health, nutrition, dietetics, audiology, psychology, and academia. Each expert receives an invitation along with an information sheet and consent form. Upon agreeing to participate, they are provided with the PTICOPE module (workbook) and the Patient Education Materials Assessment Tool for Printable Materials (PEMAT-P), a 26-item form for evaluating printed educational materials [17]. Experts will have at least two weeks to submit their feedback, after which researchers will revise the module. This process will continue iteratively until no further changes are required.

Following content validation, the finalized PTICOPE module will undergo face validation with a sample of community-dwelling older adult participants. Ten individuals from the target population, who will not participate in the study, will review the module for clarity, relevance, and ease of use. These participants will receive an invitation, including an information sheet and consent form. A group meeting will be held in a meeting room at one of the PAWE centers, where researchers will present the PTICOPE module, focusing on participants’ understanding, visual appeal, and acceptability of the intervention tasks. Two research assistants will document feedback during the session, which will be audio-recorded for accuracy. This feedback will inform final refinements to the workbook, preparing it for testing.

#### The intervention group.

Participants in the intervention group will undergo the PTICOPE intervention for 12 weeks (Table 2). Meetings will be held once a week for the first 4 weeks. During the initial meeting, participants will receive guidance on how to use the workbook, be informed of their baseline measurement outcomes to help strategize their care pathway, set personal goals, learn the exercises outlined in the workbook, and have the opportunity to ask any questions about the intervention. Participants are encouraged to contact the researchers via WhatsApp at any time throughout the week for further clarification regarding the intervention.

In the following 3 weekly meetings, to be held at the same locations, researchers will check that the workbook is being used correctly, ensure that exercises are performed according to the established goals, and address any additional concerns. After these four meetings, the first follow-up measurement will be conducted, with participants informed of their results to assist them in revising their personal goals as needed. The second and third follow-ups will continue as scheduled, with participants reminded of their appointments at the centers for further outcome measurements.

#### The control group.

Participants in the control group will receive a one-time session on IC information, including health education on the importance of exercise, a healthy diet, and self-care management. The control group will not receive the PTICOPE booklet. During the first meeting, the participants in the control group will be informed of a series of monitoring and measurement of outcomes (weeks 4, 8, and 12). A WhatsApp reminder will be sent to their mobile phone to inform them regarding the timing of the follow-up

### Outcome measures

#### Primary outcomes.

The repeated measures of the six domains of IC (cognitive decline, limited mobility [locomotor], malnutrition [Vitality], visual impairment, hearing loss, and depressive symptoms) are the primary outcomes of this study. These outcomes will be assessed at baseline and weeks 4, 8, and 12, using the WHO ICOPE screening tool. The ICOPE screening tool is a sensitive instrument to detect IC among community-dwelling older adults that does not require a substantial workforce [18]. It is used as the first step in each care pathway that covers all six core domains of IC to identify declines in IC across the six domains [19]. The psychometric properties of the ICOPE screening tools to assess IC domains among older persons from different settings have been reported in a few studies [20–22]. However, a systematic review found that the methods for assessing each of the IC domains differ substantially across studies and there is no consensus on the best method to compute an eventual global compound score to evaluate IC [23]. On the other hand, further improvements are needed in the vitality dimension of the ICOPE screening tool to enhance its sensitivity in identifying individuals at risk of malnutrition [24]. Hence, for this study, some measures of outcomes for the IC domains will be based on those validated in the Malaysian population.

We will use the validated Malay version of the Mini-Mental State Examination (MMSE) to measure cognitive function [25]. This tool includes items on orientation (5 points), registration (3 points), attention and calculation (5 points), recall (3 points), and language (9 points), with a maximum score of 30. A higher MMSE score indicates better cognitive function.

To assess locomotor or mobility function, we will use the Short Physical Performance Battery (SPPB) [26,27]. The SPPB comprises three components: gait speed (measured over 4 meters), lower limb strength (five-repetition chair rise), and static balance (side-by-side, semi-tandem, and tandem stands), with each component contributing up to 4 points. The total SPPB score ranges from 0 to 12, with higher scores indicating better locomotion.

For vitality assessment in the ICOPE screening tool, we will use questions on unintended weight loss of more than 3 kg in the past three months and appetite loss. This study will employ the validated Malay version of the short-form Mini Nutritional Assessment (MNA) [28]. The MNA has a maximum score of 14, with higher scores indicating better nutritional status.

For hearing and vision assessments, we will follow previously reported procedures, using self-reported hearing and vision impairment [29]. Participants will be categorized as having total or severe loss (0 points), moderate loss (0.5 points), or normal to mild loss (1 point).

Psychological function, as indicated by depression level, will be assessed using the validated Malay short-form Geriatric Depression Scale (GDS-15) [30]. This scale consists of 15 items with “Yes” (1 point) and “No” (0 point) responses; a higher score indicates a greater level of depression.

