Findings indicate that locomotion is the most commonly affected domain [9], and that IC decline is independently associated with increased risks of frailty, disability, falls, fractures, and immobility [10], suggesting that physiotherapy plays a critical role in maintaining and enhancing IC among older adults. Therefore, we aimed to develop a Physiotherapy-led Person-Centered Integrated Care for Older People (PTICOPE) program and evaluate its effectiveness in improving IC among older adults living in the community. We hypothesized that older adults participating in the PTICOPE program would experience significant improvements in their IC domain scores, including mobility, vitality, psychological function, cognitive function, hearing, and vision, compared with the control group. This community-based program is expected to empower older adults to achieve greater independence, enhance their functional abilities, and improve their overall well-being. Additionally, it provides guidelines for physiotherapists and other healthcare professionals working with community-dwelling older adults to regularly screen IC and monitor outcomes effectively.

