### Sample size determination

The sample size was calculated using G* Power 3 software for a repeated measures ANOVA (Baseline, week 4, week 8, week 12 measurements), aiming for a statistical power of 90%, an alpha level of 0.05, an estimated medium effect size (0.25), and a standard deviation of 2.5 for the primary outcomes and a correlation among repeated measures of 0.5. The selection of these parameters was guided by a previous study examining multicomponent exercise interventions in older adults to enhance, which reported a meaningful change of 1 point in the Short Physical Performance Battery (SPPB) as a clinically significant threshold [14].

Based on the initial analysis, a minimum of 60 participants is needed to detect a significant effect within each group. To account for potential attrition, such as participant dropouts due to withdrawal, health issues, or other factors, about 15 to 20% increase was applied. This adjustment results in a target sample size of 70 participants, divided equally into two groups (35 per group) to ensure the study maintains sufficient power to detect meaningful differences in IC changes between the intervention and control groups.

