### Data analysis

All statistical analyses will be conducted using SPSS version 29, with a significance level set at p < 0.05. Data will first undergo cleaning and analysis in SPSS, where frequency distributions and graphical representations will be used to identify outliers and missing values. For normality testing of interval data, the Kolmogorov-Smirnov and Shapiro-Wilk tests will be applied. Descriptive analysis will be conducted for participants’ demographics and baseline characteristics to describe data using tables, averages, standard deviations, ranges, frequencies, and percentages. Where appropriate, statistical comparisons between the intervention and control groups will be conducted, utilizing the independent t-test for continuous data and the Chi-square test for categorical data.

To evaluate the intervention’s impact on the primary outcomes, a repeated measures ANOVA will be conducted after data collection, as the primary outcomes involve measurements at baseline, week 4, week 8 and week 12, to evaluate the significant effects of time, intervention, and their interaction. For the secondary outcomes which involve measurements at baseline and week 12, the paired-t-test will be performed to determine the impact of the intervention.

The non-parametric tests will be performed if the main outcomes are not normally distributed that include the Friedman test and Wilcoxon signed-ranked test for the primary and secondary outcomes, respectively.

In the event of missing data due to participant dropout or incomplete data collection, an intention-to-treat (ITT) analysis will be employed to maintain the validity of the randomization process. Missing data will be managed using appropriate imputation techniques, depending on its nature and extent. For continuous variables, multiple imputation methods will be applied, while for categorical variables, methods such as last observation carried forward (LOCF) may be used. Sensitivity analyses will also be performed to assess the robustness of the results to the assumptions about the missing data.

To ensure data privacy and confidentiality, hard-copy forms collected from participants will be stored securely. All datasets will be digitized and saved on password-protected laptops, with backup copies maintained on password-protected USB drives and external hard drives. Access to these datasets is restricted to the principal researcher.

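### Six primary domains are each tested at p < 0.05 with no deciding effect, adjustment or success rule, so the error rate of the trial's conclusion is undefined and reaches about 26% if any one domain counts

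*Protocol article*

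**What the plan says.** Under Primary outcomes, "The repeated measures of the six domains of IC" (cognition, locomotion, vitality, vision, hearing and depressive symptoms) "are the primary outcomes of this study". No domain ranks above another. No composite is used, and the section remarks that "there is no consensus on the best method to compute an eventual global compound score to evaluate IC".

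Under Data analysis, one level covers everything: "All statistical analyses will be conducted using SPSS version 29, with a significance level set at p < 0.05". The primary outcomes go into a repeated measures ANOVA "to evaluate the significant effects of time, intervention, and their interaction". None of the three effects is named as the one that answers the research question.

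The Introduction states the hypothesis: participants in the programme "would experience significant improvements in their IC domain scores, including mobility, vitality, psychological function, cognitive function, hearing, and vision, compared with the control group". It lists the domains but does not say whether one, several or all must differ.

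The sample size section uses a single alpha of 0.05, 90% power, an effect size of 0.25, and "a standard deviation of 2.5 for the primary outcomes and a correlation among repeated measures of 0.5". It cites a 1-point SPPB change as a clinically meaningful threshold. The outcome and analysis sections give the SPPB no priority.

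**The concern.** With six co-equal primary outcomes at an unshared 0.05, the 5% in the sample size calculation belongs to a single test, not to the trial's conclusion. That conclusion has no stated criterion. After the data are in, a report could call the trial positive on one domain out of six, and on either of two between-arm effects within it, and still be consistent with the plan.

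The stakes are practical. Participants and the research assistants are unblinded, and hearing and vision are self-reported on three-level scales. The article also intends the findings to support a new physiotherapy approach. A chance result in one domain could therefore carry the headline.

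**Working it through.** **Inputs from the article.** Six primary domains; three effects per domain; 0.05 per test; four measurements; correlation over time 0.5; SD 2.5; effect size f = 0.25; minimum 60 and target 70 (35 per arm). **Not given:** the correlation between domains, so it is varied from 0 to 0.7 as an assumption.

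**1. The plan's own figure.** A one-group within-subject test has λ = f²·N·m/(1 − ρ). With N = 30, λ = 0.0625 × 30 × 4 / 0.5 = 15 on 3 and 87 df. Power is 90.4% at alpha 0.05 (89.2% at N = 29). Two groups of 30 give the stated 60. The figure thus uses one test at 0.05, with nothing set aside for six outcomes.

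**2. Chance of at least one p < 0.05 when there is no effect.** For k independent tests this is 1 − 0.95^k.
- One between-arm test per domain, k = 6: 1 − 0.95⁶ = 26.5%, which is 5.3 times 5%.
- Intervention or interaction counts, k = 12: 1 − 0.95¹² = 46.0%.
- One test per domain, only results favouring the intervention: 1 − 0.975⁶ = 14.1%. A single two-sided 0.05 test allows 2.5% in that direction.
- All six domains must be significant: at most 5%.

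**3. Correlated domains.** Simulated two-arm, four-time ANOVA: 30 per arm, correlation over time 0.5, no effects, 10,000 runs per setting. The r = 0 column is the exact value from step 2.

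| Counting rule | r = 0 | r = 0.3 | r = 0.5 | r = 0.7 |
|---|---|---|---|---|
| Interaction only, any domain | 26.5% | 25.0% | 21.3% | 16.6% |
| Intervention effect only, any domain | 26.5% | 24.5% | 20.3% | 16.4% |
| Intervention effect, favourable only | 14.1% | 12.1% | 10.2% | 7.8% |
| Intervention or interaction, any domain | 46.0% | 43.3% | 37.3% | 30.3% |

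**4. After a fix.** At 0.05/6 = 0.00833 with one test per domain, 1 − (1 − 0.00833)⁶ = 4.9%. If intervention and interaction both stay in play at that level, 1 − (1 − 0.00833)¹² = 9.6% (simulated 9 to 10%). Adjusting the level alone is therefore not enough. One deciding test per domain is also needed.

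**5. Power cost.** Take a 1-point SPPB difference, SD 2.5, 30 per arm, and a week-12 ANCOVA with baseline correlation 0.5. The ANCOVA is an assumption here, since the article does not plan one.
- Standard error = 2.5 × √(1 − 0.25) × √(2/30) = 0.559, so the noncentrality is 1/0.559 = 1.79 on 57 df.
- Power is 42% at 0.05 and 18% at 0.00833, the strictest Holm step.

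For the group-by-time interaction at f = 0.25 and N = 60, the cost depends on how f is defined. With the G*Power default (λ = 0.0625 × 60 × 4 / 0.5 = 30) power goes from 99.8% to 98.6%. With the SPSS definition (λ = 0.0625 × 58 × 3 = 10.875) it goes from 79% to 55%.

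**The case against.** The strongest defence is that multiplicity procedures commonly sit in an analysis plan, which is not shown here. That would answer a complaint about silence. It does not fully answer this one, because the article fixes p < 0.05 for all analyses and six co-equal primary outcomes. A later adjustment would have to change that stated level.

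The hypothesis can also be read as requiring improvement in every listed domain, in which case the error rate is not inflated at all. The text does not settle this. The primary fault is therefore the missing success rule, and the inflation is conditional on how it is filled.

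Several stronger readings are tempting but unsupported:
- **A flat five-fold error rate.** A reader might infer this from three effects on six domains. The 5.3 comes from one non-directional test per domain, independent domains and an any-one rule. It also counts results favouring control.
- **A 60% error rate.** Treating all 18 tests as independent gives 1 − 0.95¹⁸ = 60.3%. This counts six time effects, which compare no arms, whereas the hypothesis is stated against control. Eighteen tests are not assured either: non-normal primary outcomes go to the Friedman test, which does not yield three effects. The three-level vision and hearing scores may well take that route.
- **A sample size built on the SPPB alone.** The article gives a generic medium effect and an SD for the primary outcomes in the plural. The SPPB threshold is cited as guidance. One point over SD 2.5 is d = 0.4, or f = 0.20 for two groups, not 0.25.

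**Conclusion.** The point holds in a conditional form. As written, the plan has six primary outcomes, three effects each, one unshared level, and no rule that says when the trial has succeeded.

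Under an any-one-domain rule with one between-arm test per domain, the false-positive chance is up to about 26%, falling to 16 to 17% at a between-domain correlation of 0.7. For favourable results only it is about 14% down to 8%. If either between-arm effect may count, it is about 46% down to 30%. Under an all-six rule it is at most 5%.

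The existence of the gap rests on the article's own text. The percentages rest on an assumed correlation and an assumed success rule, and should be reported as ranges with those conditions.

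**What to change.** In Data analysis, name one between-arm test per domain as confirmatory, for example the group-by-time interaction or the week-12 difference between arms. Any non-parametric fallback for that test should also compare the arms. Apply Holm across the six tests at familywise 0.05, state that benefit is claimed only for domains that survive, and report the time main effect descriptively. If the investigators mean that all six domains must succeed, saying so would also close the gap, and no adjustment would then be needed.

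An optional alternative is to make the SPPB the single primary outcome, since the sample size section uses a 1-point SPPB change as its clinical anchor. That narrows the stated six-domain aim, so it is the investigators' choice.

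The article describes recruitment as not yet begun, so at that stage the change costs wording and a registry update. The statistical price is lower power per domain: about 42% to about 18% for a 1-point SPPB difference at the strictest Holm step, under the ANCOVA assumptions above.
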